## Abstract

**Background:**

Fluoropyrimidine (FP) chemotherapies are commonly prescribed for upper and lower gastrointestinal, breast and head and neck malignancies. Over 16,000 people with cancer require FP chemotherapies *per annum* in Australia. Between 10 and 40% patients experience grade 3–4 (≥ G3) toxicities that require hospital-based management ± intensive care admission. Approximately 1% of patients die secondary to FP toxicities. Prospective screening for *DPYD* gene variants (encoding the key enzyme for FP catabolism) can identify patients at risk of ≥ G3 toxicity and allow for dose adjustment prior to first FP exposure. Evidence supports this as a cost-effective method of improving patient safety and reducing healthcare burden internationally; however, no Australian data confirms its feasibility on a large scale.

**Method:**

This investigator-led, single-arm study will determine large scale feasibility of prospective *DPYD* genotyping, confirming patient safety and cost-effectiveness within the Australian health care system. 5000 patients aged 18 years and older with solid organ cancers requiring FP chemotherapy will be consented and genotyped prior to commencing treatment, and early toxicity (within 60 days) post-FP exposure will be determined. Toxicity data for *DPYD* variant carriers who have dose adjustments will be compared to the wild-type cohort and historical cohorts of carriers who did not undergo genotyping prior to FP exposure, and prospective variant carriers who do not undergo dose-adjustment. Prevalence of the four standard *DPYD* gene variants will be confirmed in an Australian population. Additionally, health economic analysis, implementation research via semi-structured interviews of patients and clinicians, and feasibility of *UGT1A1* genotyping will be conducted.

**Discussion:**

This study will determine the prevalence of *DPYD* gene variant status in Australia and its impact on FP-induced toxicity among Australians with cancer. Feasibility and cost-effectiveness for Australian health care system will be estimated to support national roll-out of prospective *DPYD* genotyping prior to FP administration. Additionally, feasibility will be confirmed with the intention of including *UGT1A1* in future pharmacogenomic panels to aid chemotherapy prescribing.

**Trial registration:**

This trial was registered with the Australian and New Zealand Cancer Trials Registry on 13th Dec 2023, ACTRN12623001301651.

**Supplementary Information:**

The online version contains supplementary material available at 10.1186/s12885-024-13122-8.

## Background

Fluoropyrimidines (FP) are commonly prescribed and variably toxic chemotherapies. Over 16,000 adult Australians receive this chemotherapy per year for the treatment of colorectal, upper gastrointestinal, breast and head and neck cancers [1]. Globally, more than 3.5million patients receive FP chemotherapies [2]. FP is delivered either as intravenous (5-fluoruracil; 5-FU) or oral (capecitabine) preparations.

Between 10–40% of patients who receive FP therapy develop severe and life-threatening (National Cancer Institute Common Terminology Criteria for Adverse Events, CTCAE grade 3 and 4) toxicities, and up to 1% die as a result of toxicity (CTCAE grade 5) [3–5]. Typical toxicities include diarrhoea, mucositis, haematological toxicities (predominantly neutropenia and thrombocytopenia), cardiotoxicity and palmar-plantar erythrodysesthesia (hand-foot syndrome) [6]. Between 31–69% of severe toxicities can be explained by a deficiency in the dihydropyrimidine dehydrogenase (DPD) enzyme, encoded by the *DPYD* gene (Fig. 1) [7, 8]. DPD catabolises circulating 5-FU, allowing excretion of inactive metabolites [9]. People who are DPD deficient lack the capacity to adequately catabolise circulating 5-FU, creating a supratherapeutic build-up of active drug and excessive toxicities as a result. Testing for DPD functional activity is difficult and surrogate tests such as *DPYD* genotyping have been developed to overcome this, though no test has yet been devised that can accurately identify all patients at risk of severe FP toxicities [10].

**Fig. 1 Fig1:**
[figure not shown]
Metabolic Pathway of Fluoropyrimidines, adapted from White [8]. Legend: * Fluoropyrimidine chemotherapeutic agents, ^ Genes. Enzymes: CES; carboxyl esterase, CDA; cytodine deaminsae, TP; thymidine phosphorylase, TS; thymidylate synthase, DPD; dihydropyrimidine dehydrogenase, DHP; dihydropyrimidinase, B-UP; beta-ureidopropionase. Metabolites: 5’dFCR; 5’-deoxyfluorocytidine riboside, 5’dFUR; 5’-deoxyfluorouridine, FUH2; dihydrofluorouracil, FUPA; fluoro-beta-ureidopropionate, FBAL; fluoro-beta-alanine, FUMP; fluorouridine monophosphate, FUDP; fluorouridine diphosphate, FUTP; fluorouridine triphosphate, FUDR; fluorodeoxyuridine, FdUMP; fluorodeoxyuridine monophosphate, FdUDP; fluorodeoxyuridine diphosphate, FdUTP; fluorodeoxyuridine triphosphate, dUMP; deoxyuridine monophosphate, dTMP; deoxythymidine monophosphate. Genes: DPYD encodes DPD, TYMS encodes TS

Throughout Europe, four clinically significant *DPYD* variants are increasingly screened prior to administration of FP agents, endorsed by the European Medicines Agency and local government bodies [11–16]. People found to carry *DPYD* variants (c.1905 + 1G > A, (*DPYD* *2A), c.2846A > T, c.1679 T > G and c.1236G > A/HapB3), have decreased function of their alleles to make DPD enzyme, resulting in DPD deficiency and FP toxicity when standard FP doses are administered [17, 18] (Table 1). Approximately 8% of the European-Caucasian population carry one of these four variants, and other variants of significance in non-Caucasian populations are emerging and are likely to become incorporated in standard screening panels as supporting data expands [19, 20]. There is a limited understanding of *DPYD* expression in Aboriginal and Torres Strait Islander communities, although a small genomic study from a single indigenous population in the Tiwi Islands suggests that *DPYD* and *UGT1A1* expression differs from Caucasian data [21, 22].

**Table 1 Tab1:** Clinically significant DPYD variants: variant allele frequency, DPD enzyme function, and relative-risk of FP-related toxicity

*DPYD* variant (rs number)	Variant Allele Frequency^a^ [3]	Allele function	Relative Risk of Toxicity at standard FP dose, (95% CI) [17, 18]
c.1905 + 1G > A, *DPYD**2A (rs3918290)	0.9–1.5%	No function	2.85 (1.75–4.62)
c.1679 T > G (rs55886062)	0.1–0.2%	No function	4.40 (2.08–9.30)
c.2846A > T (rs67376798)	1.1–1.5%	Partial function	3.02 (2.22–4.10)
c.1236G > A/ HapB3 (rs56038477)	4.3–4.7%	Partial function	1.72 (1.22–2.42)

^a^European Caucasian data

Screening for *DPYD* variants prior to FP exposure allows an opportunity to dose-adjust FP chemotherapy regimens to make treatment more tolerable. Collaborative guidelines are in place to guide dosing decisions centred around which *DPYD* variants patients carry and tolerance of treatment, including those published by EviQ that guide dosing decisions in Australia [23]. While these guidelines do not mandate upfront *DPYD* screening, they support clinician-patient discussion and shared decision making.

A similar gene-drug relationship exists for uridine-diphosphate-glucuronosyltransferase family 1 (*UGT1A1*) gene and irinotecan chemotherapy. Irinotecan is typically prescribed in the management of pancreaticobiliary, other upper gastrointestinal, colorectal, sarcoma and lung cancers. Each year, approximately 2000 Australian cancer patients are prescribed irinotecan. Up to 40% of patients administered standard doses of irinotecan will develop grade 3–4 toxicities including diarrhoea and neutropenia [24]. Approximately 9% of European-Caucasians carry a *UGT1A1* variant; however, there is substantial ethnic variability throughout Asia (up to 41% variant carriers) [24]. There are 3 commonly significant variants; *UGT1A1**6, *28 and *37, with *28 associated with the most significant functional deficit. Current guidelines recommend carriers homozygous for *UGT1A1* *28 and certain compound heterozygotes start with 70% of the normal irinotecan dose, but availability of supporting data outside of Europe is limited [24].

Pharmacogenomic (PGx) screening for *DPYD* variants has been embraced in Europe with positive data indicating improved patient safety and cost-effectiveness [17, 25, 26]. It is not yet known if a PGx screening intervention of this magnitude can be successfully and sustainably implemented in Australia. Consideration must be given to the geographical, institutional and ethnic differences in Australia as compared to Europe, including Aboriginal and Torres Strait Islander communities. To date, Australia has not been so forthcoming with support for an upfront screening strategy [8]. Glewis et al. (2024) report barriers to implementation, as described by Australian oncology clinicians, including the out-of-pocket (OOP) expense for patients and the perceived long turn-around time (TAT) of genotyping results [27]. Currently, Australian patients self-fund genotyping which excludes those without the means to afford testing.

Feasibility data from a pilot study (awaiting publication) conducted in regional Australia confirms a turnaround-time (TAT), on par with feasibility data from metropolitan institutions in the United Kingdom [28]. Furthermore, this pilot study evaluated clinician stakeholder perceptions of barriers and found similar themes to Glewis (2024), as well as lack of staffing and resources (education and support) [27]. An outstanding enabler within this pilot study was the degree of clinician motivation to improve the current system for the benefit of patient safety and delivery of innovative and high-quality healthcare.

Current gaps in knowledge regarding *DPYD* screening in Australia include:Will dose personalisation improve safety outcomes/ decrease toxicity for *DPYD* variant carriers who undergo dose personalisation in Australian practice?Is upfront *DPYD* screening cost-effective?What is the prevalence of the common 4 *DPYD* variants in the Australian population? Does this prevalence differ in non-Caucasian populations? Are there additional *DPYD* variants that are clinically significant that we must consider for an Australian-centric pharmacogenomic screening panel?Is *UGT1A1* genotyping feasible?What other factors can explain severe FP toxicity?

### Objectives and endpoints

GeneScreen 5-FU will confirm the evidence needed to successfully implement upfront *DPYD* PGx screening in Australia by demonstrating clinical impact, safety and cost-effectiveness. The primary objective is to establish an upfront PGx screening and dose modification pathway to guide dose personalisation and reduce FP-induced toxicity, improving patient safety. Secondary endpoints include confirmation of prevalence of *DPYD* variants in Australia, feasibility of genotyping, analysis of the cost-effectiveness of genetic screening and determination of cancer outcomes for *DPYD* carriers (Disease-Free Survival, DFS; Progression-Free Survival, PFS; Overall Survival, OS). Tertiary and translational endpoints will explore the feasibility of *UGT1A1* genotyping and explore the genomic traits of patients who develop severe toxicity in the absence of *DPYD* variants (and vice versa) (Table 2).

**Table 2 Tab2:** GeneScreen 5-FU objectives and endpoints

**Objectives**	**Endpoints**
**Primary**	
Determine efficacy of upfront *DPYD* PGx-guided dose-adjustment on FP safety and toxicity of carriers of clinically significant *DPYD* variant alleles.	a) Frequency of serious FP-related toxicity in patients receiving FP chemotherapies: - Grade 3 and 4 toxicity (CTCAE v5), hospitalisations (including presentations not resulting in admission), ICU admissions and death (CTCAE v5, Grade 5). [5] - Case Report Forms (CRF) for toxicities Grade 3-5. b) Frequency of serious FP-related toxicity in *DPYD*variant carrier patientsreceiving FP chemotherapies: - Using same metrics as above.
Develop and implement strategies to address enablers and barriers identified in the feasibility study.	Using validated framework and including patient and clinician interviews [29, 30]
Determine cost-effectiveness of upfront* DPYD* genotyping and personalised dosing and estimate healthcare benefits of full implementation of *DPYD PGx*-guided dose-adjustment in an Australian population.	a) Health economic and cost-effectiveness analysis of upfront *DPYD* screening and PGx-guided dose-adjustments / individualisation. b) Apply health economic modelling to illustrate cost burden and cost-effectiveness of pre-emptive *DPYD* screening on health care services.
**Secondary Objectives**	
Determine feasibility of PGx screening and dose-adjustment.	a) Feasibility of *DPYD* genotyping and utility of dose recommendation guidelines: - TAT for genotyping. - Proportion of variant allele carriers who undergo dose-adjustment. Identification and exploration of adherence / deviations from dose-adjustment guidelines.
Confirm prevalence of clinically significant *DPYD *variants within the Australian community.	Measure frequency of each of the 4 *DPYD *variants c.1905+1G>A (rs3918290), c.2846A>T (rs67376798), c.1679T>G (rs55886062) and c.1236G>A (rs56038477).
Deliver a scientifically sound PGx protocol for pre-treatment genotyping that can be adopted into pathology laboratories across Australia.	Evaluate effectiveness of implementation research strategies using validated framework [29, 30]
[29, 30] Determine cancer outcomes for *DPYD* variant carriers with dose-adjusted FP compared to current standard of care.	Measure long-term outcomes including disease-free survival (DFS), progression-free survival (PFS) and overall survival (OS)
**Tertiary / Translational Objectives**^a^	
Identify *UGT1A1* variants (**6*, **28* and **37*) in patients receiving irinotecan and explore feasibility of expansion of a PGx panel to include *UGT1A1 *genotyping.	Determine *UGT1A1 *variant allele frequency and establish feasibility of genotyping pathway.
Explore other factors contributing to severe toxicity in patients not carrying the aforementioned *DPYD* variant alleles.	a) Consider genomic polymorphisms, within the *DPYD* gene or elsewhere, other downstream regulators and enzymes along the FP metabolic pathway to formulate translational investigations. b) Evaluation of DPD enzyme activity in selected cases: - Confirm that genotype correlates with phenotype measures (UH2/U concentration ratio, pharmacokinetics)

*CTCAE* Common terminology criteria for adverse events, *DFS* Disease-free survival, *DPYD* Dihydropyrimidine dehydrogenase (gene), *FP* Fluoropyrimidine, *OS* Overall survival, *PFS* Progression-free survival, *PGx* Pharmacogenomic, *TAT* Turn-around time, *UGT1A1* Uridine-diphosphate-glucuronosyltransferase family 1

^a^Translational endpoints only partially covered by current funding

## Methods/design

This is a single arm, non-randomised, multicentre prospective study. In recognition of the strong international data that show benefit for PGx-guided dosing, it is considered unethical for us to conduct a randomised controlled trial to directly compare the implementation and non- implementation of PGx-guided dosing. It is a collaborative, investigator-led initiative supported by a trial committee comprising researchers from most states in Australia.

### Study population

We aim to enrol 5000 patients from hospitals across multiple states in Australia and including metropolitan, regional and rural cancer services. Eligible participants are 18 years and older with solid organ malignancies intended to receive FP chemotherapies (either 5-FU or capecitabine) and/or irinotecan chemotherapy as part of either curative or palliative cancer management either as single agents or in combination. Patients must be able to provide informed consent and capable of providing a blood sample for genotyping. Exclusion criteria include those who have received prior treatment with FP chemotherapies, or who decline consent or blood collection. Patients who are pregnant or breastfeeding are also excluded, as are those already enrolled in other clinical trials that are likely to influence toxicity outcomes.

### Intervention

*DPYD* genotyping will be prospectively conducted in all patients prior to commencement of FP chemotherapies. Genotyping pathology services will be pre-determined by participating sites. Clinically significant *DPYD* variants will include c.1905 + 1G > A (rs3918290), c.2846A > T (rs67376798), c.1679 T > G (rs55886062) and c.1236G > A (rs56038477) (Supp Fig. 1). Patients found to carry one or more clinically significant variants will undergo dose-adjustment of FP chemotherapy prior to first administration, in accordance with eviQ guidelines (Supp Tables 1 and 2) [23].

◦ Heterozygote carriers of a single specified *DPYD* variant should receive a 50% dose-reduction prior to first FP exposure◦ Following this administration, patients should be reassessed and FP dose further down-titrated or ceased in response to G3-4 toxicity, or up-titrated for those who experienced minor or no toxicities. Suggested increment for titration is ± 12.5% (of the 100% recommended dose), as suggested by EviQ.◦ Patients who carry two variants (either compound heterozygote or homozygote carriers) should be dosed on an individual basis and may need to avoid FP administration altogether.

Data will be collected on all patients and will include specific datapoints for *DPYD* variant carriers who undergo dose-reductions to explore adherence to guidelines versus alternative dose-adjustment decisions. Bio-banked specimens from patients who do not have a pre-specified *DPYD* variant but experience ≥ G3 toxicities will undergo further exploratory genotyping. A subset of samples from patients intended to receive irinotecan chemotherapy will be batched and genotyped for clinically significant *UGT1A1* variants (*6 (*UGT1A1* c.211G > A), *28 A(TA)6TAA > A(TA)7TAA promoter), *37 (A(TA)6TAA > A(TA)8TAA promoter). Any *UGT1A1* genotype-guided dose-adjustment will be at clinician discretion. *UGT1A1* genotyping is for assessment of feasibility only. Data monitoring will be intermittently conducted by the trial management committee.

### Implementation sub-study intervention

Qualitative interviews will be conducted with a convenience sample of 20 to 40 patients and clinicians involved in PGx screening, with the sample size dependent on achieving sufficient breadth and depth as is favoured over saturation in this methodology [29]. Interviews with patients will be conducted following enrolment, genotyping and at least first cycle of chemotherapy. Clinicians will be contacted throughout the trial. This will be decided by the research team through discussions parallel to recruitment and data collection. Participants will be asked to complete semi-structured qualitative interviews over the telephone or teleconferencing which will be up to 45 min in length. Patient interviews will explore the degree to which people offered genotyping were aware of and understood the purpose of genetic testing and dose-personalisation in the trial, experiences of *DPYD* variant carriers who received *DPYD* genotype-guided dose-personalisation, including information needs around*,* and lived-experiences of dose-personalisation throughout treatment. Clinician interviews will explore the experiences of using *DPYD* PGx-guided dose-personalisation, including reasons for adjusting/not adjusting the dose, intention to continue using *DPYD* PGx-guided dose-personalisation, and barriers and facilitators to this prescribing method.

Interview recordings will be transcribed, deidentified and imported into a qualitative data analysis software package for analysis. Interview and focus group transcripts will be deidentified prior to analysis. Only members of the research team who are not involved in patient care will be involved in the analysis. Reflexive thematic analysis will be conducted to explore the commonalities and dissimilarities within and across the data, and reflexive practice will be employed to acknowledge and account for any subjectivities (bias) in the data analysis [30]. These findings will be used to optimise the PGx screening process and provide tailored support and educational resources.

### Clinical assessment, data collection and storage

The clinical assessment schedule is summarised below (Table 3), where implementation is included in the assessment table and is discussed separately below.

**Table 3 Tab3:** GeneScreen 5-FU assessment schedule

Assessment Time-point	Data points collected	Comments
*Baseline*	Patient and cancer demographics FP chemotherapy data *DPYD* genotype status	FP containing regimens Chemotherapy indication
*Post-first FP dose*	Patient metrics FP dose and adjustments FP related toxicities Hospitalisations, ICU admissions, treatment-related death	G3-4 toxicities Time in hospital Time in ICU G5 toxicity-related deaths Dose reduction data
*Subsequent FP administration* *(capped at 60 days post-first dose)*	Patient metrics FP dose and adjustments FP related toxicities Hospitalisations, ICU admissions, treatment-related death	G3-4 toxicities Time in in hospital Time in ICU G5 toxicity-related deaths Dose reduction data
*No fixed time point*	Patient and clinician semi-structured interviews	Exploration of patient/clinician experience of genotyping process Clinician satisfaction with education/support resources, facilitators/barriers to ongoing use
*Follow-up*	Cancer outcomes reports at 6-month intervals up to 5 years post-FP	Disease-free survival (DFS) Progression-free survival (PFS) Overall survival (OS) All cause mortality

Initial assessment will include patient demographics, tumour data and chemotherapy indication (curative/palliative). Chemotherapy regimens and FP dosing will also be collected. Clinical parameters including height and weight and haematological results prior to each cycle will be recorded. Dates of *DPYD* sample collection and results will be recorded, as well as the variant carrier status (including *UGT1A1* where applicable).

Data from patients will be collected from clinical presentations within the first 60 days of their first FP dose to identify grade 3 and 4 toxicities requiring hospital presentation with or without admission, ICU admissions and deaths related to FP toxicities. Grading will be in accordance with the current CTCAEv5 [5]. For patients who carry *DPYD* variants and undergo dose-adjustments, FP dosing trends and adherence to/utility of the guidelines will be recorded. Patient follow-up data will be collected for 5 years to determine long-term cancer outcomes (DFS, PFS and OS). Data will be collected, de-identified and stored on a secure REDCap database. Patient samples will be de-identified and bio-banked.

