#### Historical comparators

We felt it was unethical to have a control group of patients with *DPYD* variants who undergo standard FP dose administration due to the well described increased risk of toxicity within this population [9, 10]. Therefore, comparator populations for this project will include:Current standard of care, as assessed by a retrospective review of 500 consecutive cases in NSW [31].Contemporaneous cases without these *DPYD* variants treated with standard doses,*DPYD* variant carriers in this study that do not receive PGx-guided dose-adjustment, and.Patients treated in European cohorts whereby *DPYD* variant carriers were treated with a 25% or 50% FP dose reduction.

Background ≥ G3 toxicity in an ungenotyped population is approximately 17.4%, and in *DPYD* variant carriers without FP dose adjustment is reported to be 39–61% [8, 31]. Sub-analyses for each *DPYD* variant will be included.

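### The data-collection text limits grade 3–4 events to those needing a hospital presentation, in conflict with the endpoint table, assessment schedule, hypothesis and analysis; external comparisons could be biased if this is not reconciled

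*Protocol article*

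**What the plan says.** Under Clinical assessment, data collection and storage, the protocol article says that data from clinical presentations in the first 60 days after the first fluoropyrimidine (FP) dose will be collected "to identify grade 3 and 4 toxicities requiring hospital presentation with or without admission, ICU admissions and deaths related to FP toxicities". On its ordinary reading, the hospital condition restricts which grade 3–4 events are sought.

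Other parts of the article define or record the same outcome without that condition:

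- **Table 2, primary endpoint:** "Grade 3 and 4 toxicity (CTCAE v5), hospitalisations (including presentations not resulting in admission), ICU admissions and death (CTCAE v5, Grade 5"). Hospital presentation stands beside grade 3–4 toxicity as a component of its own. The same cell also specifies "Case Report Forms (CRF) for toxicities Grade 3-5".
- **Table 3, after the first dose and at later doses to 60 days:** "FP related toxicities Hospitalisations, ICU admissions, treatment-related death". The comments column gives grade 3–4 toxicities and time in hospital as separate items.
- **The paragraph after Table 3:** "Clinical parameters including height and weight and haematological results prior to each cycle will be recorded".
- **Statistical hypotheses and Statistical analyses:** the fall from 60% to 35%, Fisher's exact test and the logistic regression all concern toxicity of grade 3 or higher, without qualification.
- **Historical comparators:** the background rate of grade 3 or higher toxicity is 17.4% in ungenotyped patients, and the rate in "variant carriers without FP dose adjustment is reported to be 39–61" per cent. Neither figure comes with a description of how events were found.

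**The concern.** Some grade 3–4 events need not bring a patient to hospital. The Background names neutropenia, thrombocytopenia and hand-foot syndrome among the typical FP toxicities. A grade 3–4 neutropenia seen on a pre-cycle count, with no hospital presentation, is an event under Table 2 but not under the data-collection text. Sites that work from different parts of the document could count differently.

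The trial has a single arm, and its stated test compares carriers with historical controls. Randomisation cannot balance a difference in how events are ascertained. If the trial counts a narrower set of events than the external cohort did, the observed rate falls with no effect of genotype-guided dosing, and the error favours the intervention. A larger sample does not remove such a bias.

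**Working it through.** **1. The plan's own figure.** Inputs from Statistical hypotheses and Sample size determination: 60% against 35%, 80% power, 5% level (sidedness not stated), 70 per arm.

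The two-sided normal approximation uses a mean rate of (0.60 + 0.35)/2 = 0.475:

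n = [1.96·√(2·0.475·0.525) + 0.8416·√(0.60·0.40 + 0.35·0.65)]² / 0.25² = (1.384 + 0.575)² / 0.0625 ≈ 61.4, so 62 per arm.

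With the continuity correction:

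(61.4/4)·[1 + √(1 + 4/(61.4·0.25))]² ≈ 69.2, so 70 per arm.

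The stated 70 is reproduced. The exact power of Fisher's test at 70 per arm is 81.0%. The sample size is not in dispute here.

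**2. What a capture difference does.** Let p be the true rate of grade 3 or higher toxicity, the same in both groups (no effect). Let f_T and f_C be the shares of those patients counted in the trial and in the external cohort. The observed rates are p·f_T and p·f_C, so the spurious relative rate is f_T/f_C. With equal shares it is 1 and there is no bias.

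**3. Assumed range.** The documents give neither share. Set f_C = 1 (the external cohort counted everything) and let f_T = f, the share leading to a hospital presentation. The table gives the probability of a significant result in the direction of a reduction, with the two-sided exact Fisher test at 5%, 70 per arm and no true effect. The base rates are the hypothesis value (60%) and the lower end of the quoted carrier range (39%).

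| f (assumed) | Observed rate, base 60% | False reduction | Observed rate, base 39% | False reduction |
|---|---|---|---|---|
| 1.0 | 60% | 1.6% | 39% | 1.6% |
| 0.9 | 54% | 7.8% | 35.1% | 4.8% |
| 0.8 | 48% | 24% | 31.2% | 12% |
| 0.7 | 42% | 51% | 27.3% | 26% |
| 0.6 | 36% | 77% | 23.4% | 45% |

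The 1.6% in the first row is the error rate in one direction with equal capture; it lies below 2.5% because Fisher's test is conservative.

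**4. Which comparisons are exposed.** Historical comparators and Table 4 list four groups. Two are external: the retrospective review of 500 cases and the European cohorts. The other two, patients without the variants and carriers without dose adjustment, are enrolled in this study and their events are collected in the same way. The mismatch described here concerns only the external pair.

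**The case against.** The strongest reply is that the article, taken as a whole, does not fix hospital-only capture. Table 2 plans case report forms for grade 3–5 toxicity with no hospital condition. Table 3 lists grade 3–4 toxicities apart from hospitalisations, and pre-cycle haematology is recorded. One sentence reads more narrowly, and a condensed article may leave rules on event sources to the full protocol. This stands in part. A reader might infer that toxicity is collected only from hospital presentations and that the neutropenia example would be lost; the tables and the recorded blood counts do not support that. What remains is a contradiction about which events count towards the primary endpoint, and that is more than omitted detail.

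The second reply is that the external cohorts may have used a similar rule. The Abstract ties grade 3–4 toxicity to hospital-based management. This also stands, as a reason for caution: a reader might infer that the trial under-counts relative to its benchmarks, but their ascertainment is not described. The Abstract does not settle the matter either, because the Background gives the same 10–40% range for grade 3–4 toxicity with no hospital condition.

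Third, the size rests on two unknown capture shares, and full capture in the control is as much an assumption as f. That is correct, so the table illustrates a range and does not estimate the bias.

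A reader might also infer that known carriers, watched more closely, would present to hospital less and so be under-counted. Nothing in the article describes such monitoring, and closer observation could equally raise the number of detected events.

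**Conclusion.** The data-collection text contradicts Tables 2 and 3, the hypothesis and the analysis on whether a grade 3–4 event without a hospital presentation counts. Followed as written, it would measure a narrower endpoint than the one hypothesised and tested.

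The consequence is conditional. Only if the narrow text is followed and an external cohort counted more completely does that comparison lean towards a reduction. Under the assumptions of full control capture, a 60% base rate, 70 per arm and no true effect, 90%, 80% and 70% capture give false-reduction chances of about 8%, 24% and 51%, against 1.6% with equal capture. At a 39% base rate the figures are about 5%, 12% and 26%. The documents do not show that the bias is present, and the definitional mismatch does not reach the comparators within the study. The passages should be reconciled before the external comparisons are made.

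**What to change.** Amend the data-collection sentence to match Tables 2 and 3: every FP-related CTCAE v5 event of grade 3 or higher within 60 days of the first FP dose counts, from any source, including clinic review and the pre-cycle haematology already recorded. Report hospital presentation, admission and ICU admission as separate components.

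In each external comparison, apply the same definition on both sides. Where an external source captured only hospital events, compare the hospital-presentation component. State how each external source ascertained its events.

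The cost is a text edit and some extra abstraction of clinic notes. Forms for grade 3–5 toxicity and collection of blood counts are already planned, and the sample size does not change.
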